## Abstract

**Introduction:**

Cardiorespiratory fitness (CRF) testing is routinely performed by most armed and tactical forces around the world as part of their recruitment process for new members or simply as an annual examination of their personnel. A 2-mile run (2_MR_) test is among the most commonly used. However, as it is performed outdoors, weather, climate, and terrain can influence the results and often limit the maximum performance. Also, this test has been shown to be difficult for individuals because the pacing strategy is self-paced. As such, it does not reflect the real situation on the battlefield, where most activities are externally driven by the environment and the enemy. Therefore, we believe that the 30-15 Intermittent Fitness Test (30-15_IFT_) may be a suitable tool for measuring CRF and battle readiness of military personnel. Moreover, given the importance of visual attention to military personnel we aim to investigate the differences in visual attention between better and less physically prepared infantry members and its corresponding response to maximal endurance running test.

**Methods and analysis:**

This randomized cross-over study using a within-subjects test-retest design will enroll 32 infantry members of the Slovenian Armed Forces. To investigate the reliability and validity of the 30-15_IFT_ test, an incremental treadmill test (TR), a 2_MR_ test, and two identical 30-15_IFT_ will be performed in randomized order. Additionally, participants will be subsequently divided into two groups based on their score on the Army Physical Fitness Test (APFT), whereas differences in visual attention will be assessed by using the d2 test. The primary analysis will assess differences in key physiological outcomes between the different CRF tests (TR vs. 2_MR_ vs. 30-15_IFT_). In addition, the relative reliability of all dependent variables between two 30-15_IFT_ trials will be estimated by interclass correlation coefficient (ICC), while relationship between maximal oxygen uptake, heart rate and maximal running speed of 30-15_IFT_, TR and 2_MR_ will be assessed using Pearson’s correlation.

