## Materials and methods

### Study design

The proposed study is a part of a greater project entitled “Enhancement of Physical and Combat Preparedness of Slovenian Armed Force Members; “(original language, Slo: “Dvig telesne in bojne pripravljenosti pripadnikov Slovenske vojske”), which was funded by the Slovenian Research Agency (ARRS) and Slovenian Ministry of Defense (project No. V5-2106; project manager: Assoc. [name]. [name]; principal investigator: Assist. [name]. [name]). This is a randomized cross-over study using a within-subjects test-retest design. To test the current hypothesis, an incremental treadmill test (TR), a 2_MR_ test, and two identical 30-15_IFT_ will be performed in the population of SAF soldiers. For a better understanding of the following text, the term participant is used instead of soldier. The present study will be conducted over a maximum period of 2 weeks per participant. Participants will be instructed to visit the laboratory four times at least 72 h apart. At the first visit, they will be familiarized with the experimental procedures and asked to sign a written informed consent form to participate in the study. Then, participants will be randomly assigned to four experimental conditions (i.e., TR, 2_MR_ and two 30-15_IFT_ running tests).

Additionally, participants will be subsequently divided into two groups based on their score on the APFT (score ranging from 1 to 5). Thus, the higher-scoring group (HSG) is defined as an APFT score of ≥ than 4; and the lower-scoring group (LSG) is defined as an APFT score of ≤ than 2.

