### Participants

Thirty-two SAF infantry members (males, *N* = 27) will be recruited for the proposed study. Inclusion criteria are: age 18–40 years, both male and female SAF infantry members who are performing regular military tasks on daily basis, with no history of injuries in the last 6 months prior to recruitment, have not reported any musculoskeletal pain, with no history of chronic musculoskeletal, metabolic, pulmonary, neurological and cardiovascular diseases. Participants will be instructed to avoid any strenuous physical activity for at least 3 days prior to the start of the first testing session and during the course of study, which will be monitored by their superiors. They will be requested to refrain from consuming ergogenic substances and caffeinated beverages prior to the tests. Before the initial assessment on each testing day, a brief meeting will be held to explain the study protocol in detail.

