#### Incremental treadmill test

After 5 min of baseline measurements, while standing on the treadmill (HP Cosmos, Germany), the participants will warm up at 8 km/h run and constant gradient of 1% inclination (Jones and Doust, 1996). Then, they will execute the actual test by running until volitional exhaustion where the running speed will be increased progressively by 2 km/h per minute. The achievement of VO_2max_ was identified as the plateauing of VO_2_ (<2.1 ml/kg/min decrease) despite an increase in workload (Poole and Richardson, 1997). If the above-stated criterion was not fulfilled, the participants will be asked to perform a further constant-speed test equal or higher than the highest speed achieved at the end of the incremental test, as recommended (Rossiter et al., 2006). Throughout the test, respiratory gases will be continuously measured breath-by-breath and reduced to 10-s averages (Borszcz et al., 2018). MRS will be determined as the minimal running velocity that elicited VO_2_max over a period of 30 s.

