#### 2-mile run test

The 2_MR_ will be used as a continuous field test to assess CRF. It will be performed on a 400-m synthetic athletic track with the supervision of the research team. Participants will be required to complete the 2-mile run course without any physical help in the shortest time possible. At the start, all participants will line up behind the starting line. On the command “go,” the clock will start. They will begin running at their own pace. Although walking is authorized, it is strongly discouraged. Immediately after competition of the test, the time achieved will be reported to the nearest to 0.01 s and used for further analysis. The heart rate at the end of the 2-mile test will be considered the maximal heart rate achieved in the test. Additionally, the perceived effort of the trial will be recorded at the end of the test using the modified Borg visual scale (Borg, 1982).

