#### Statistical analysis

All data will be presented as mean ± SD with 90% confidence interval limits (90% CI). All statistical analysis will be conducted using the SPSS statistical software (version 27.0, IBM Inc., Chicago, United States). Descriptive statistics will be used to summarize demographic characteristics of participants and outcomes. Normality od the data will be confirmed by using the visual inspection of histogram and Q-Q plot and analytically by Shapiro-Wilk test, while the homogeneity of variances of normally distributed variables will be tested by using Levene’s test.

Differences in key physiological outcomes between the different CRF tests (TR vs. 2_MR_ vs. 30-15_IFT_) will be assessed by One-Way ANOVA analysis. The relative reliability of all dependent variables between two 30-15_IFT_ trials will be estimated using the ICC, two-way random effects model (consistency type). ICC values will be classified as very high if > 0.90, high if between 0.70 and 0.89, and moderate if between 0.50 and 0.69. The following criteria will be used to declare good reliability: CV < 5% and ICC > 0.69 (Buchheit et al., 2011). In addition, the standard error of the estimate (SEM) and the coefficient of variation (CV) will be calculated as measures of absolute reliability, indicating the within-subject variation, as previously proposed (Hopkins, 2000). To further address the reliability of the data, bias and random error will be calculated, followed by the minimal detectable change (MDC). To test the usefulness of the IFT, the spreadsheet provided by Hopkins will be used (Hopkins). Usefulness will be determined by comparing the smallest worthwhile change (SWC) with the typical error of measurement (TE) and will be interpreted as follows: “Marginal” (TE > SWC), “OK” (TE = SWC) and “Good” (TE < SWC) (Hopkins, 2007).

Relationship between VO_2max_, HR_peak_ and end running speed of 30-15_IFT_, TR, and 2_MR_ will be assessed using Pearson’s correlation (r). Also, the relationship between VO_2max_ obtained from TR, 2_MR_, and 30-15_IFT_ will be investigated. The following thresholds of the correlation coefficient will be used to assess the magnitude of the relationships analyzed: weak ≤ 0.35; 0.36 ≤ moderate < 0.67; 0.68 ≤ high < 1 (Taylor, 1990).

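### Both 30-15IFT trials are randomised among the four sessions with no stated pairing or common interval, so the typical error, MDC and bias would average over unlike retest conditions

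*Protocol article*

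**What the plan says.** The abstract (Methods and analysis) introduces the testing as serving both reliability and validity, and says that "an incremental treadmill test (TR), a 2_MR_ test, and two identical 30-15_IFT_ will be performed in randomized order". The Study design section agrees: "participants will be randomly assigned to four experimental conditions (i.e., TR, 2_MR_ and two 30-15_IFT_ running tests".

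Spacing is bounded on two sides. "Participants will be instructed to visit the laboratory four times at least 72 h apart" sets a minimum, and "The present study will be conducted over a maximum period of 2 weeks per participant" sets a ceiling. Neither fixes the interval between the two 30-15IFT trials.

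Outside exertion is controlled: participants must "avoid any strenuous physical activity for at least 3 days prior to the start of the first testing session and during the course of study". The study's own tests are demanding. The treadmill test means "running until volitional exhaustion where the running speed will be increased progressively by 2 km/h per minute", with a further constant-speed bout for those who show no plateau. In the 2-mile run participants must "complete the 2-mile run course without any physical help in the shortest time possible".

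The Statistical analysis section says that "The relative reliability of all dependent variables between two 30-15_IFT_ trials will be estimated using the ICC", using a two-way random-effects model of the consistency type. The SEM, CV, bias, random error, MDC and the rating of typical error against the smallest worthwhile change are also planned as reliability measures. No term or stratum for interval, session position or intervening test is described. Good reliability is declared at CV < 5% and ICC > 0.69.

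**The concern.** Random order is sound for comparing three different tests, because it spreads order effects over them. A test-retest estimate has a different need: the interval and the exertion between the two trials should be alike for everyone, so that the error term describes one defined condition.

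The article treats the two 30-15IFT sessions as two more items to be shuffled. One participant may repeat the test at the next visit, while another repeats it after a treadmill test and a 2-mile run. A consistency ICC removes only the mean difference between trial 1 and trial 2. A shift that depends on the order drawn stays in the error term, and the reported bias becomes an average over different situations.

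The figures most exposed are the typical error, the MDC, the bias and the usefulness rating. Coaches would rely on these to judge whether an individual soldier has changed.

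**Working it through.** The plan gives no figure of its own on this point, so there is none to reproduce.

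**Inputs from the protocol article.** Four sessions (TR, 2MR and two 30-15IFT) in random order; at least 72 h (3 days) between visits; at most 2 weeks per participant; 32 participants.

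**Assumptions.** One test per visit, and all orders equally likely. The article does not describe the randomisation scheme.

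**Step 1: orders.** Distinct orders of {TR, 2MR, IFT, IFT}: 4!/2! = 12. With a first-to-last span of 13–14 days and every gap at least 3 days, the longest retest interval is the span minus 3 days for each gap lying outside the pair.

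| Tests between the IFT trials | Orders | Share | Expected of 32 | Retest interval (days) |
|---|---|---|---|---|
| None | 6 | 50% | 16 | 3 to about 7–8 |
| One (TR in 2 orders, 2MR in 2) | 4 | 33% | 10.7 | 6 to about 10–11 |
| Both | 2 | 17% | 5.3 | 9 to about 13–14 |

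Under simple randomisation the number of consecutive pairs would be 12 or fewer, or 20 or more, in about 22% of studies (binomial, n = 32, p = 0.5).

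**Step 2: a shift in the non-consecutive half.** Assume a true typical error of 0.3 km/h, and that trial 2 moves by d in the 50% of participants with a test in between. The shift adds 0.5 × 0.5 × d² = 0.25d² to the variance of the between-trial difference. Typical error is SD(difference)/√2, so its square rises by 0.125d².

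- d = 0.5 km/h (one stage): √(0.09 + 0.03125) = 0.348, or +16%.
- d = 0.25 km/h: √(0.09 + 0.0078) = 0.313, or +4%.
- d = 0: 0.300, no change.

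If MDC is a fixed multiple of the typical error, it rises in the same proportion. At d = 0.5 the expected bias is 0.5 × 0.5 = 0.25 km/h. That describes neither the half with no shift nor the half with 0.5.

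**Step 3: gradual drift instead of a shift.** Assume between-subject SD 1.0 km/h, trial error 0.3 km/h, and individual drift of SD τ per session. The squared typical error is 0.09 + L × τ²/2, where L is the number of sessions from trial 1 to trial 2. The mean of L over the random orders is 0.5 × 1 + (1/3) × 2 + (1/6) × 3 = 1.67. At τ = 0.3:

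- always consecutive: √(0.09 + 0.045) = 0.37;
- random mix: √(0.09 + 0.075) = 0.41;
- always first and last: √(0.09 + 0.135) = 0.47.

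Simulated ICCs for τ = 0, 0.1, 0.2 and 0.3 are 0.92, 0.91, 0.90 and 0.88 for always-consecutive trials, and 0.92, 0.91, 0.89 and 0.87 for the random mix. The difference is at most about 0.02, and all values are well above 0.69.

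**Step 4: the CV criterion.** The larger typical error in step 2, taken against the 8 km/h opening stage, is 0.348/8 = 4.35%. It stays below 5% for running speed at any end speed of 8 km/h or more, given the assumed 0.3 km/h.

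**Step 5: effect of pairing on the three-test comparison.** With IFT-IFT as a block, TR and 2MR keep a mean session position of 2.5. The first 30-15IFT trial moves from (1+1+1+2+2+3)/6 = 1.67 to (1+2+3)/3 = 2.0, closer to the other two tests.

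**The case against.** The strongest reply is that random order serves the analysis the abstract calls primary, the comparison of the three tests, with reliability listed after it. There are also real safeguards: at least 72 h of recovery, a two-week limit, no other strenuous activity under the supervision of superiors, a common morning-to-early-afternoon testing window, and one timeline for every test (Table 1). Nothing in the document shows that fatigue or practice lasts beyond 72 h.

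Much of this stands, and it rules out three stronger readings.

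- A reader might infer that the order is wholly unrestricted. The article says only that it is random. A restricted or balanced list may exist in the full protocol, so the 50/33/17% split is conditional.
- A reader might infer that a finding of high reliability would hinge on which orders were drawn. The working does not support this: the ICC barely moves, the CV criterion for running speed holds under the assumed values, and the mixture makes typical error and MDC larger than consecutive testing would. That is conservative for the authors' hypothesis.
- A reader might infer that the usefulness rating would change. The article gives no smallest worthwhile change in figures, so this cannot be shown.

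The trade-off argument itself does not stand. Randomising blocks keeps the random order of the three tests, and step 5 shows no loss of balance for that comparison.

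**Conclusion.** The point holds as a cheap design improvement, not as an error that overturns a conclusion. As described, the two 30-15IFT trials have no common retest condition: zero, one or two maximal tests may lie between them, over 3 to about 13–14 days. The planned analysis pools these without distinction.

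The consequence is a typical error, CV, MDC, bias and usefulness rating that average over unlike conditions. Typical error and MDC would be inflated by about 4% to 16% under assumed shifts of 0.25 to 0.5 km/h and a true typical error of 0.3 km/h, and not at all without carry-over, practice or drift. The shares rest on equally likely orders. Every effect size is assumed, because the document gives none.

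**What to change.** Keep the two 30-15IFT sessions on consecutive visits, with one common interval for all participants and the same start time for both trials. Randomise, in balanced numbers, the six orders of the three blocks TR, 2MR and IFT-IFT. The common interval has to be stated, because consecutive visits alone still allow 3 to about 7–8 days. State also that the first 30-15IFT trial enters the three-test comparison, so that each test counts as one administration.

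The cost is a new randomisation list and a sentence or two in the protocol, with no extra visit, test or participant. There are two small downsides. Scheduling is slightly less flexible. Trial 1 is still preceded by zero, one or two maximal tests, so the block scheme equalises what happens between the trials but not what comes before the first; balanced numbers spread this evenly over the orders.

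If the list can no longer be changed, report each participant's retest interval and number of intervening tests, and give typical error and bias separately for consecutive and non-consecutive pairs as a sensitivity analysis.

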
To date, no study has examined the reliability and validity of the 30-15_IFT_ compared to a standard continuous incremental running test and/or a 2_MR_ in infantry members of the Slovenian Armed Forces (SAF). From a practical perspective, it would be of great interest to SAF personnel to provide their strength and conditioning coaches with a valuable measure of CRF to determine and monitor the readiness of SAF infantry members. In addition, we aimed to investigate differences in visual attention between better and less physically prepared infantry members and its corresponding response to maximal endurance running test. Therefore, we hypothesized that the 30-15_IFT_ will prove to be a highly reliable and valid measure of CRF while other parameters such as maximal heart rate (HR_*max*_) and maximal running speed (MRS_*IFT*_) will be valuable indicators of intermittent fitness data for prescribing, monitoring, and optimizing high-intensity interval training in this population. Moreover, it is expected that when compared to less prepared infantry members, a better prepared infantry member will have fewer decline of visual attention following maximal endurance running test.

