### Sample size calculation and statistical analysis

#### Sample size

In the conceptualization phase of the study, we conducted an *a priori* power analysis for the estimated interclass correlation coefficient (ICC) as previously recommended (Bujang and Baharum, 2017). Based on previous studies with similar aim we expected to find high to nearly perfect ICC for the reliability of 30-15_IFT_ test (Buchheit, 2008; Buchheit et al., 2011). Therefore, with power of 0.90, two-tiled α = 0.05, and four observations per subject a minimum sample size of 6 subjects showed to be sufficient to detect a value of ≥ 0.80 for the ICC.

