In addition, to determine performance differences between two groups of SAF members, a repeated-measures General Linear Model will be used for main physiological parameters estimated from different tests (TR vs. 2_MR_ vs. 30-15_IFT_) as within-subject factor, whereas groups (HSG vs. LSG) will be used as between-subject factors. Partial eta squared (η^2^) values of 0.01, 0.06, and 0.14 rated difference as small, moderate and high, respectively (Cohen, 1988). Statistical significance for all analysis conducted will be accepted at *p* ≤ 0.05.

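### The primary difference test cannot by itself show that the 30-15IFT is valid, and no acceptable difference from the treadmill is set

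*Protocol article*

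**What the plan says.** The last paragraph of the Introduction gives the hypothesis: "we hypothesized that the 30-15_IFT_ will prove to be a highly reliable and valid measure of CRF". The Introduction also treats the incremental treadmill run as the reference standard for VO2max.

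The abstract (Methods and analysis) declares: "The primary analysis will assess differences in key physiological outcomes between the different CRF tests". Under Statistical analysis these differences "will be assessed by One-Way ANOVA analysis". That section ends with one threshold for everything: "Statistical significance for all analysis conducted will be accepted at" p ≤ 0.05. It also commits to 90% confidence limits for all data.

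Two other groups of statistics bear on the hypothesis:

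- **Reliability.** ICC, CV, SEM, bias and random error, minimal detectable change and the usefulness rating are introduced for the reliability or usefulness of the 30-15IFT. The criteria for good reliability are CV < 5% and ICC > 0.69.
- **Association.** Pearson's r is planned between the tests for VO2max, peak heart rate and end running speed, with bands for weak, moderate and high. The abstract lists it as additional to the primary analysis.

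The article gives no acceptable difference between 30-15IFT and treadmill, no between-method agreement statistic, and no rule for reading either result of the ANOVA.

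**The concern.** For VO2max and peak heart rate, a claim that a field test is valid against a reference standard is largely a claim that the two give close enough values. A test of no difference is built to reject closeness, not to support it. When p > 0.05, the data may simply be too noisy to show a difference that is there. When p ≤ 0.05, a precise test may have been flagged for a bias nobody would care about. Without a stated acceptable difference, neither result can be translated into valid or not valid, and the choice of what counts as close enough is left until the data have been seen.

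This is not a detail waiting for an analysis plan. The article itself names the primary analysis, its method and its significance level, and the mismatch lies in that choice.

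**Working it through.** **1. The plan's own figure.** The only sample-size figure is a minimum of 6 for the ICC ("with power of 0.90", two-sided α = 0.05, k = 4, ICC 0.80). With a null ICC of 0 (assumed, since none is stated), C0 = 1/(1 + 4 × 0.80/0.20) = 1/17. Then n = 1 + 2(1.960 + 1.282)² × 4 / [(ln C0)² × 3] = 4.49, rounded up to 5. Exact F-test power is 92% at 5 and 96% at 6, so the stated 6 is reproduced to within one subject. It concerns reliability only; no figure is given for the between-test comparison.

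**2. What the difference test reports.** From the document: the study "will enroll 32 infantry members of the Slovenian Armed Forces", each performing every test, and α = 0.05. Assumed: a paired analysis, and all biases and SDs of differences (ml/kg/min). With 31 df the critical value is 2.040, δ = bias × √32 / SD, and P(not different) = F(2.040; 31, δ) − F(−2.040; 31, δ), where F is the noncentral t distribution function.

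| True bias | SD of differences | δ | Not different | Different |
|---|---|---|---|---|
| 2.5 | 3 | 4.71 | 0.5% | 99.5% |
| 2.5 | 5 | 2.83 | 22% | 78% |
| 2.5 | 8 | 1.77 | 60% | 40% |
| 1 | 2 | 2.83 | 22% | 78% |

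The second and fourth rows are identical because the test responds only to the ratio of bias to SD. It cannot separate a bias of 2.5 in a noisy test from a bias of 1 in a precise one.

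**3. Dependence on the form of ANOVA.** The article does not say that the ANOVA is repeated-measures. Three-test simulations assumed a between-subject SD of 6 and a reference error SD of 1.5.

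- Repeated-measures, bias 1: not different in 5%, 24%, 56% and 80% of studies as the new test's error SD goes 0.5, 1.5, 3, 6. This is the pattern of step 2.
- Independent groups, bias 2: not different in 94–100% over the same range of error. In this form a precise test rarely fails on a trivial bias; most biases of this size go undetected.

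**4. What the correlations add.** Under the same assumptions the expected r is 36 / √[(36 + 1.5²)(36 + e²)], with e the new test's error SD. At e = 0.5 this is 36/√(38.25 × 36.25) = 0.97; at e = 6 it is 36/√(38.25 × 72) = 0.69. So r does fall as noise rises. The bias does not appear in the formula: adding a constant, or multiplying by one, leaves r unchanged. An SD of differences of 5 means e² = 25 − 2.25 = 22.75 and r = 36/√(38.25 × 58.75) = 0.76, inside the plan's high band whatever the bias.

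**5. The same data judged against a margin.** Two one-sided 5% tests are equivalent to asking whether the 90% CI, mean ± 1.696 × SD/√32, lies inside the margin. The margin of ±2.5 is assumed for illustration only.

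| True bias | SD | Equivalence shown |
|---|---|---|
| 2.5 | any | at most 5% |
| 1 | 2 | 99% |
| 0 | 3 / 5 / 8 | 99.7% / 74% / 11% |
| 1 | 5 | 49% |

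The two cases that step 2 could not separate (bias 2.5 with SD 5, bias 1 with SD 2) now give 5% and 99%. At SD 8 the CI half-width is 1.696 × 8/5.657 = 2.40, so almost no estimate could fit inside ±2.5.

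**6. Mean against individual agreement.** At SD 5 the 95% limits of agreement are bias ± 1.96 × 5 = ± 9.8, although an unbiased test would show mean equivalence 74% of the time. The mean difference alone is therefore not enough.

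**The case against.** A reader might infer that the authors will call the 30-15IFT valid if the ANOVA is non-significant, so that imprecision is rewarded. The documents do not support this. They give no decision rule for either result, and the planned correlations would tend to expose a noisy test: under the assumptions in step 4, an SD of differences of 8 gives r = 36/√(38.25 × 97.75) = 0.59, only moderate on the plan's scale. That part of the objection stands, and the point is limited to what the primary test cannot answer.

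It can also be said that validity need not mean equal values. The article promises an adopted formula for VO2max, and recalibration could absorb a constant bias. It also makes comparing three protocols an aim in itself, which a difference analysis serves. Both are fair, and they are reasons to keep the three-test comparison and the correlations. But a bias has to be estimated before it can be absorbed, and no between-method estimate with a criterion is planned. The bias statistic in the plan is introduced for reliability.

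Finally, the claim that noisy tests escape while precise ones are flagged needs a paired or repeated-measures analysis, which the text does not specify. Step 3 shows what changes otherwise; under neither form does the result establish agreement.

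**Conclusion.** The concern holds in this form: the declared primary analysis does not by itself address the validity hypothesis, and the rest of the plan does not close the gap. The correlations cannot detect constant or proportional bias, and the agreement-type statistics belong to the two 30-15IFT trials.

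The percentages are illustrations. The biases, SDs, between-subject SD and margin are all assumed, because the article gives none of them. The logical point depends on none of them. This is an inexpensive improvement to the choice of analysis; it does not show that the study will reach a wrong conclusion.

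**What to change.** For VO2max and peak heart rate, base the validity conclusion on the paired mean difference, 30-15IFT minus treadmill, with its 90% CI, naming which of the two 30-15IFT trials supplies the value. Judge the CI against an acceptable difference that the sponsor justifies before seeing the data. The margin should not be borrowed from the CV < 5% criterion, which concerns repeatability of one test and not bias between methods. Report 95% limits of agreement alongside. Keep the three-test comparison, including the 2-mile run, and the correlations as supporting analyses. Do not apply the margin to running speed, where equality is not expected.

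The cost is some analysis wording and a justified margin for each of the two outcomes. No further visits or measurements are needed, and 90% intervals are already planned. The downside is that with a large SD of differences the 32 participants may leave equivalence inconclusive: about 49% power at bias 1, SD 5 and margin 2.5, all assumed. The plan should say so, and should state that an inconclusive interval shows neither agreement nor disagreement.
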